### **Tertiary Endpoint**

Metaanalysis of Vaccine Efficacy: We will compare combined active vaccination from VAC046 and VAC047, with combined control vaccination from VAC046 and VAC047, for time to first episode of *P.falciparum* infection, defined as 2 or more consecutive blood samples confirmed positive by PCR for *P.falciparum*.

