#### Rationale

An important next step in the clinical development of ChAd63 / MVA ME-TRAP heterologous prime-boost immunisation is to assess efficacy in the field. The VAC046 clinical trial (SSC Number 2116, Kenya) is planned to commence in 2012 to assess efficacy, immunogenicity and safety of this vaccination strategy in adults in Kenya. The vaccines will be given by the preferred route, intramuscular, and at the preferred adult doses,  $5 \times 10^{10}$  vp of ChAd63 ME-TRAP and  $2 \times 10^8$  vp of MVA ME-TRAP, in the standard prime-boost regimen of ChAd63 ME-TRAP followed eight weeks later by MVA ME-TRAP.

The VAC047 study proposed here will be undertaken in parallel using the same vaccination regimen and overall study design as VAC046, extending the Phase II development of the vaccination strategy to a separate malaria endemic setting. The investigators seek to combine the results of the two studies in a metaanalysis to evaluate the efficacy of the vaccination regimen in a larger sample of adults living in malaria-endemic areas.

There are plans to undertake a clinical trial to evaluate the efficacy of ChAd63 / MVA ME-TRAP prime boost immunization in infants in a malaria endemic area, if justified by the results of these trials. The most efficacious regimen incorporating ChAd63 ME-TRAP and MVA ME-TRAP would be selected for this trial.

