## **13. STATISTICS**

### **Sample Size Considerations**

The efficacious malaria vaccine RTS,S/AS02 has been subjected to sporozoite challenge studies in non-immune volunteers (62) as well as field trials in adults in the Gambia (30). In sporozoite challenge, RTS,S/AS02 appears to give 32% sterile protection and 30% partial protection. Efficacy was higher in semi-immune adults in field studies, with 70% during the first 9 weeks of follow up.

Vaccine efficacy of ChAd63/MVA ME-TRAP in sporozoite challenge studies in Oxford was 21% sterile protection with 36% partial protection. We therefore consider it plausible that ChAd63/MVA ME-TRAP might show 50% efficacy in field studies of adults.

Assuming 50% efficacy of vaccination, with an estimated 70% local incidence of malaria by PCR during the follow up period, we expect 93% power to detect, at  $p=0.05$ , an efficacy of 50% and 77% power to detect an efficacy of 40% with 100 volunteers. Allowing for up to 20 volunteers to be lost to follow up, our sample size would be 120.

Below we tabulate the power obtained with differing vaccine efficacies and rates of PCR positivity, assuming  $p=0.05$  and 100 evaluable volunteers completing the study.

It should be noted that the incidence of asymptomatic parasite carriage detected by qPCR was taken to be 70% on the basis of two observations in the literature.

- a) The qPCR technique was used in the Gambia to assess the impact of prospective vaccines on 102 volunteers. The results of follow-up over five months showed that 71% of the volunteers became positive again at some time or other during follow-up (Imoukhuede et al. 2007; see paper attached). We also include a second article by Andrews et al. highlighting the excellent sensitivity of this real-time PCR method.

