***Efficacy***

Efficacy will be analysed both ITT and ATP. Cox regression model analysis of incidence of PCR positivity will allow assessment of the time to first episode as the primary outcome. Various thresholds for PCR positivity will be included for comparison. Age, bed net use and location of residence will be used as covariates. Immunological responses will also be examined as covariates to look for correlates of immunity. These analyses will also be undertaken as a metaanalysis of the combined results of VAC046 and VAC047.

The full analysis plan will be approved by the DSMB before implementation.

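### The pooled VAC046/VAC047 comparison is worded as combined arms with no trial factor; it should be stratified by trial explicitly

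*Protocol*

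**What the plan says.** Under Endpoints, the Tertiary Endpoint is headed as a meta-analysis and defined as follows: "We will compare combined active vaccination from VAC046 and VAC047, with combined control vaccination from VAC046 and VAC047", for time to first PCR-confirmed infection. No trial term, stratum or method of combining trials is named.

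The Efficacy paragraph of the Statistics section sets the model: "Cox regression model analysis of incidence of PCR positivity will allow assessment of the time to first episode as the primary outcome". It adds: "Age, bed net use and location of residence will be used as covariates". It then extends this to the pooled data: "These analyses will also be undertaken as a metaanalysis of the combined results of VAC046 and VAC047". How location is to be coded when the trials are put together is not stated.

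The Rationale places VAC046 in Kenya, says that both trials share the regimen and overall design, and describes VAC047 as "extending the Phase II development of the vaccination strategy to a separate malaria endemic setting". VAC046's sample size, allocation ratio and expected infection risk are not given. For Senegal, Sample Size Considerations works "with an estimated 70% local incidence of malaria by PCR during the follow up period".

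**The concern.** A meta-analysis combines contrasts made within each trial. The Tertiary Endpoint instead describes one combined active group against one combined control group. Read literally, that is a Cox model with one baseline hazard for Kenya and Senegal, although the protocol itself calls them separate endemic settings.

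Two things can go wrong if trial is left out. First, when baseline hazards differ, volunteers at the high-risk site leave the risk set faster among controls than among vaccinees. The remaining controls become a lower-risk mix than the remaining vaccinees, and the hazard ratio drifts towards 1. Second, if the proportion vaccinated differs between the trials, trial becomes an ordinary confounder.

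At stake are the accuracy and power of an analysis that was added in order to gain a larger sample.

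**Working it through.** **1. The plan's own figure.** No power is stated for the pooled analysis. For VAC047 alone the protocol claims 93% power for "an efficacy of 50% and 77% power to detect an efficacy of 40% with 100 volunteers". With 50 per arm, control risk 0.70 and vaccinee risk 0.70 × (1 − 0.50) = 0.35, or 0.70 × (1 − 0.40) = 0.42, two-sided 0.05, Fisher's exact test gives 93.1% and 77.0%. All twelve cells of Table 8 reproduce to within one point. Table 8 therefore treats efficacy as a reduction in risk. The steps below use the hazard ratio, because the planned model is Cox, so their powers are not on the Table 8 scale.

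**2. Inputs for the pooled check.**
- From the protocol: Senegal control risk 70%, efficacy 50% (here HR = 0.5), 1:1 allocation and 100 evaluable in VAC047.
- Assumed: 1:1 allocation and equal size in VAC046, the same hazard ratio in both trials, exponential infection times, and a Kenyan control risk of 60% down to 10%.

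**3. The mechanism in one case (70% vs 10%).** Set follow-up to length 1. The control hazards are −ln(0.3) = 1.204 and −ln(0.9) = 0.105; the vaccinee hazards are half of these, 0.602 and 0.0527. At the start the ratio of average hazards is 0.50. At the end of follow-up:
- controls still at risk: (0.3 × 1.204 + 0.9 × 0.105) / (0.3 + 0.9) = 0.380
- vaccinees still at risk: (0.548 × 0.602 + 0.949 × 0.0527) / (0.548 + 0.949) = 0.254

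The ratio has drifted to 0.254 / 0.380 = 0.67. A Cox model that omits trial averages over this drift.

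**4. Large-sample limit.** Write S₁, S₀ for the pooled proportions at risk and f₁, f₀ for the pooled infection densities in vaccinees and controls. The Cox estimate β without trial solves

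∫ [ f₁ − (f₁ + f₀) · S₁e^β / (S₁e^β + S₀) ] dt = 0.

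| Assumed Kenyan control risk | Pooled VE, trial omitted (true 50%) |
|---|---|
| 60% | 49.8% |
| 50% | 49.2% |
| 30% | 47.2% |
| 20% | 45.7% |
| 10% | 43.7% |

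**5. Simulation** (4,000 runs per row, 50 per arm per trial, two-sided 0.05; "u" unstratified, "s" stratified by trial).

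| Kenyan risk | VE u / s | Power u / s | Rejection with no effect u / s |
|---|---|---|---|
| 50% | 49.7 / 50.5% | 91.8 / 92.8% | 4.3 / 4.8% |
| 30% | 47.2 / 50.0% | 82.2 / 86.6% | 3.6 / 5.4% |
| 10% | 43.9 / 50.2% | 64.0 / 78.5% | 1.1 / 4.6% |

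**6. Unequal allocation.** Suppose VAC046 were of equal size but allocated 2:1. With control risks of 70% in Senegal and 30% in Kenya, omitting trial gives VE 56.6% for a true 50%, and +17.8% when there is no effect. With the risks swapped it gives 35.7% and −22.0%.

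**7. Location as a trial indicator.** With 40,000 simulated subjects, HR 0.5, 1:1 allocation and Kenyan risks of 50, 30, 20 and 10%, a Cox model with a trial main effect and one stratified by trial gave the same VE: 49.1, 49.6, 51.6 and 49.8%. With strongly opposed hazard shapes at the two sites (Weibull shape 2 or 3 against 0.5), they differed by 0.8 to 1.6 points, in either direction.

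**The case against.** A reader might infer that the pooled analysis ignores trial and so biases efficacy towards zero. The documents do not support that reading.

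- *Ignoring trial.* The Efficacy section puts location of residence in the model and then applies the same analyses to the combined data. Nobody living in Guédiawaye is in the Kenyan trial, so location coded by place across both countries contains trial, and step 7 shows that this is nearly as good as strata. This stands. What remains is that the coding is not stated. District codes reused within each trial, for example, would not separate the countries.
- *Towards zero.* That direction needs equal allocation. VAC046's ratio can only be inferred from its shared overall design, and step 6 shows error in both directions if the ratios differ. With 1:1 allocation in both trials there is no bias when the vaccine has no effect. A crude pooled risk ratio, given a common risk ratio, is not attenuated either.
- *Size.* At 70% vs 30%, expected infections are 50 × (0.70 + 0.30) = 50 in controls and 50 × (0.452 + 0.163) ≈ 31 in vaccinees. With about 81 events the standard error is 2/√81 = 0.22, and the 95% interval for a VE of 50% is roughly 23 to 68%. A shift of 2.8 points is small beside that.
- *Importance.* It is also tempting to say that this analysis will decide whether the infant trial goes ahead, because VAC047 alone is weak. The Rationale ties the infant trial to the results of both trials and gives the pooled estimate no deciding role, and the protocol states 93% power for VAC047.
- *Place.* The coding of a covariate may properly sit in the full analysis plan, which is not shown. That is fair, but the combined-arm contrast is fixed in the protocol's own endpoint definition.

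**Conclusion.** The point holds in a limited form. The endpoint definition describes a combined-arm contrast with no trial factor, and the Efficacy section repairs this only if location is coded across both countries, which is not said. If trial were left out, a true efficacy of 50% would be understated by 50 − 49.2 = 0.8, 50 − 47.2 = 2.8 and 50 − 43.7 = 6.3 points at Kenyan control risks of 50%, 30% and 10%. The simulated power loss is 1.0, 4.4 and 14.5 points. These sizes rest on the assumed Kenyan risks, equal trial sizes, 1:1 allocation in both trials, a common hazard ratio and exponential times. With unequal allocation neither the direction nor the size carries over. The analysis is tertiary, so this is an improvement worth making rather than a fault in the trial's main result.

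**What to change.** Align the Tertiary Endpoint and the Efficacy paragraph on one sentence, for example: *Individual data from VAC046 and VAC047 will be analysed in a Cox model stratified by trial, with the same endpoint and covariates; the pooled hazard ratio, each trial's hazard ratio and a trial-by-vaccine interaction will be reported.*

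Stratification gives each country its own baseline hazard, protects against differing allocation ratios, and makes the result independent of how location is coded. It costs wording only: no extra participants, samples or follow-up, and no change to the primary analysis.

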## **10. SAFETY**

Safety oversight will be the responsibility of the investigators and the independent Data Safety and Monitoring Board (DSMB).

### **Discontinuation of the study**

Both arms of the study will be discontinued in the event of the following:

- New scientific information is published to indicate that the volunteers in the study are being exposed to undue risks as a result of administration of investigational medicinal products (IMPs) or as a result of the follow –up schedule.
- Serious concern about the safety of the IMPs arise as a result of vaccine related serious adverse event(SAE)s occurring in the subjects enrolled in this or any other ongoing study of the IMPs.
- For any other reason at the discretion of the Principal investigators.

### **Data collection**

Adverse events will be documented in individual case report forms (CRFs) for each volunteer. They will be recorded under two headings; local and general. There will be separate sections for the concomitant medication, concomitant vaccinations, non-serious adverse event documentation, serious adverse event documentation and study conclusion. Any deviations from the study protocol will be documented. Case report forms will be kept securely, and HIV status will not be recorded in the CRF.

### **Definitions of adverse event categories**

#### **Adverse event**

Any untoward medical occurrence in a patient or clinical investigation subject occurring in any phase of the clinical study whether or not considered related to the vaccine. This includes an exacerbation of pre-existing conditions or events, intercurrent illnesses, or vaccine or drug interaction. Anticipated day-to-day fluctuations of pre-existing conditions, including the disease under study, that do not represent a clinically significant exacerbation will not be considered adverse events. Discrete episodes of chronic conditions occurring during a study period will be reported as adverse events in order to assess changes in frequency or severity.

Adverse events will be documented in terms of a medical diagnosis(es). When this is not possible, the adverse event will be documented in terms of signs and symptoms observed by the investigator or reported by the subject at each study visit.

Pre-existing conditions or signs and/or symptoms (including any which are not recognised at study entry but are recognised during the study period) present in a subject prior to the start of the study will be recorded on the Medical History form.

#### **Adverse reactions**

In the pre-approval clinical experience with a new medicinal product or its new usages, particularly as the therapeutic dose(s) may not be established, all noxious and unintended responses to a medicinal product related to any dose should be considered adverse reactions.

### **Serious Adverse Events (SAE)**

A serious adverse event is any untoward medical occurrence that at any dose:

- results in death,
- is life-threatening,

**Note:** The term “life-threatening” in the definition of “serious” refers to an event in which the patient was at risk of death at the time of the event; it does not refer to an event which hypothetically might have caused death if it were more severe.

- requires inpatient hospitalisation or prolongation of existing hospitalisation,
- results in persistent or significant disability/incapacity, or
- is a congenital anomaly/birth defect.

Medical and scientific judgment should be exercised in deciding whether expedited reporting is appropriate in other situations, such as important medical events that may not be immediately life-threatening or result in death or hospitalisation but may jeopardise the patient or may require intervention to prevent one of the other outcomes listed in the definition above. These should also usually be considered serious.

SAEs are subject to expedited reporting to the sponsor, ethics committee and local safety monitor (see below).

### **Suspected Unexpected Serious Adverse Reactions (SUSAR)**

An adverse reaction, the nature or severity of which is not anticipated based on the applicable product information (*e.g.*, Investigator's Brochure for an unapproved investigational medicinal product) is considered as an unexpected adverse drug reaction. Where the adverse reaction is also considered to have a possible, probable or definite relationship with the vaccine, and also meets the criteria for a serious adverse reaction, it is termed a Suspected Unexpected Serious Adverse Reaction (SUSAR). These events are subject to expedited reporting as for SAEs, and are also reported to the regulatory authority (see below).

### **Collection of Adverse events**

At each post-vaccination visit an examination will be documented including an examination of local reactions at the injection site. The largest diameter through the injection site of any redness will be recorded in millimetres. The largest diameter through the injection site of local swelling, defined as a more generalized swelling of the deltoid muscle will be recorded in millimetres. Severity of these local findings will be graded using the scale given in Table 4.

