**Table 1: Solicited local and general adverse events to be documented in the CRF**

| Adverse events         |                                                   |
|-------------------------------|---------------------------------------------------|
| Local (injection site) | Pain at the injection site                        |
|                               | Redness at the injection site                     |
|                               | Swelling at injection site                        |
|                               | Warmth at the injection site                      |
| General                | Documented fever (axillary temperature > 37.5° C) |
|                               | Symptoms of feverishness                          |
|                               | Malaise                                           |
|                               | Arthralgia                                        |
|                               | Headache                                          |
|                               | Myalgia                                           |
|                               | Nausea / vomiting                                 |
|                               | Other(specify)                                    |

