***Safety data***

All reactogenicity analyses will be on an intention to treat basis, comparing control to malaria vaccine regimen. The frequency of adverse events, changes in ALT, plasma creatinine, haemoglobin, white cell count, platelet values will be described by time and vaccine group.

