### **MVA ME-TRAP**

More than 700 volunteers have received MVA ME-TRAP in the United Kingdom (UK), Senegal and the Gambia. Most volunteers developed erythema (or discolouration in African skin) and swelling post vaccination which in the majority of cases was mild to moderate in nature. This was accompanied by discomfort, warmth, itching and scaling which typically resolved to a faint flat papule. Intramuscular administration of MVA ME-TRAP has significantly less local reactogenicity than intradermal. Local AEs are likely to be mild in nature and should resolve rapidly, although there is the possibility of moderate arm pain in some cases. Common systemic adverse events post MVA vectored vaccines include headache, feverishness, myalgia, arthralgia, fatigue, and malaise. Generally volunteers report a transient flu like illness within 24 hours of vaccination with MVA which resolves completely. It is anticipated that the majority of systemic adverse events post MVA ME-TRAP will be mild or moderate in intensity. No vaccine related serious adverse events have been seen with MVA ME-TRAP.

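### Local swelling is defined as a generalised deltoid swelling, which conflicts with the solicited event and its diameter bands, so focal swellings may be missed or graded inconsistently (minor)

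*Protocol*

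**What the plan says.** Three places in the protocol describe how swelling is captured.

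- **The event.** Table 1 in Section 9 lists four solicited local reactions for the CRF: pain, redness, warmth and "Swelling at injection site".
- **The definition and measurement.** Section 10, Collection of Adverse events, calls for an examination at each post-vaccination visit. What is measured is "The largest diameter through the injection site of local swelling", and the same sentence then restricts the term: "local swelling, defined as a more generalized swelling of the deltoid muscle will be recorded in millimetres".
- **The grade.** The section continues: "Severity of these local findings will be graded using the scale given in Table 4". Part a of that table (the grading Table 4 in Section 10, not the visit schedule that carries the same number in Section 9) gives swelling Grade 0 at 0 mm, Grade 1 below 20 mm, Grade 2 from 20 to 50 mm and Grade 3 above 50 mm.

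Safety and reactogenicity form a secondary objective (Section 8). Under Safety data in Section 13, adverse event frequencies "will be described by time and vaccine group".

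**The concern.** The definition, the listed event and the scale do not describe the same thing. A raised area confined to the injection site is plainly the event in Table 1, and its size falls naturally within the lower bands of the scale. It is not a generalised swelling of the deltoid. An assessor who works from the definition may not treat it as local swelling at all, while one who works from Table 1 will measure and grade it.

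What is at stake is the completeness and consistency of one of the four solicited local reactions compared between arms. This is a rule for collecting data, so a later analysis plan cannot repair it: a diameter that was never taken cannot be recovered. The protocol's own summary of experience with MVA ME-TRAP mentions "swelling post vaccination which in the majority of cases was mild to moderate in nature". The lower grades therefore matter for this product, and a narrow definition would put those grades at most risk.

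**Working it through.** The protocol states no figure to reproduce, so the check is a comparison of its texts.

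**1. Event against definition.** Table 1 names swelling at the injection site without restriction. Section 10 restricts swelling to a more generalised form. The sentence just before it places no such limit on redness: any redness is measured. Reading the two sentences together, a careful assessor could fairly conclude that not every swelling counts.

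**2. Is there another item for focal swelling?** The definition says more generalised but does not say than what. Neither Table 1 nor the grading tables in Section 10 contain an induration or focal-swelling item. A focal swelling that fails the definition has no other solicited local row.

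**3. Definition against scale.** The two diameter scales in the grading Table 4 are:

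| Grade | Swelling (mm) | Redness (mm) |
|---|---|---|
| 1 | under 20 | under 50 |
| 2 | 20 to 50 | 50 to 100 |
| 3 | over 50 | over 100 |

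The swelling cut-offs are 20/50 = 0.4 and 50/100 = 0.5 of those for redness. The sign described as generalised across a muscle thus has the tighter bands. The bands suit a focal swelling, and the definition does not.

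**4. Two illustrative swellings, two readings.** Take focal swellings of 15 mm and 40 mm at the site.

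- Following Table 1 and the scale: 15 mm is Grade 1 and 40 mm is Grade 2.
- Following the definition literally: neither is local swelling, so no diameter is called for. The protocol does not say what to enter instead.

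Both assessors can claim to have followed the protocol.

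**5. Who assesses.** Follow-up in Section 9 has study clinicians and field workers recording local events, and Section 10 gives the investigator the severity assessment of solicited signs. Under Study groups, field workers are blinded and clinical investigators are not. The decision whether a swelling exists is therefore left partly to unblinded judgement.

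**6. Size.** The expected number of focal swellings missed in the vaccine arm would be 60 × p × q, where p is the proportion of vaccinees with a focal swelling and q is the proportion of those assessed under the literal reading. Only the 60 is in the protocol, so no number follows.

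**The case against.** The case for leaving the text alone has real content.

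- **The measurement is anchored to the site.** The diameter is taken through the injection site, and the examination is of local reactions there. That agrees with Table 1 and makes the lenient reading natural. This stands as a reason why many assessors would grade correctly. It does not remove the restricting clause.
- **There are other routes into the record.** Follow-up in Section 9 has swelling recorded as absent, mild, moderate or severe. Section 10 asks subjects at each visit about local side effects and documents unsolicited events. So a focal swelling need not vanish. It may still miss the diameter and the solicited grade.
- **Earlier experience may not carry over.** The MVA ME-TRAP text adds that intramuscular dosing is less locally reactogenic than intradermal, and all doses here are intramuscular. The ChAd63 ME-TRAP text puts swelling among the less frequent local events. The definition of swelling used in the earlier studies is not given. This stands, and it is one reason no frequency can be put on the problem.
- **The consequence is small.** The data are descriptive, the same wording applies to both arms, and neither the criteria for delaying vaccination nor those for discontinuing the study refer to a swelling grade. This also stands.

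A reader might go further and infer that small swellings will be scored Grade 0 and that those meeting the definition will tend to be Grade 3. The protocol supports neither. Grade 0 is reserved for 0 mm, any measured swelling below 20 mm is Grade 1, and nothing says a focal swelling is scored 0. A drift to Grade 3 would need a typical size for a generalised deltoid swelling, which the protocol does not give; nor does more generalised necessarily mean the whole muscle.

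**Conclusion.** The point holds as a minor one. The definition of local swelling in Section 10 conflicts with the solicited event in Table 1 and fits poorly with the swelling bands in the grading table. Applied literally, it excludes focal injection-site swelling, so such swellings may be missed or graded inconsistently between assessors, some of them unblinded.

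This rests on the wording alone and needs no clinical assumption. How often it would happen cannot be derived: it depends on how many assessors follow the clause literally and how frequent focal swelling is with intramuscular dosing, and the protocol gives neither. Any count of lost events or shift in the percentage with swelling would be arithmetic on invented rates. The effect is limited to the descriptive reactogenicity summary; the primary efficacy comparison and the sample size do not depend on it.

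**What to change.** In Section 10, Collection of Adverse events, and in the CRF guidance, define local swelling as any swelling at the injection site, measured at its largest diameter and graded on the existing swelling scale, to match Table 1. If generalised swelling of the deltoid is also of interest, record it as a separate yes/no item outside the diameter scale.

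The cost is one sentence in the protocol and a matching line in the CRF guidance, plus one tick-box if the separate item is wanted. It needs no extra visit and no new diameter measurement. It should be in place before data collection starts, since unrecorded diameters cannot be restored afterwards.
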